#### Data sources

We plan to use a Residential History File approach to identify our primary effectiveness outcome (facility-free days). The Residential History File concatenates VA, Medicare (including Medicare Advantage), and Medicaid claims to describe longitudinal episodes of care for individual Veterans across VA and non-VA settings [65, 66]. This approach uses VA and Medicare data to identify acute care hospitalizations and the Minimum Data Set (collected for every post-acute and long-term care nursing home stay for Veterans in the VA, Medicare, and Medicaid files) to identify days in these facilities versus outside these facilities as well as mortality data.

#### Quantitative evaluation

We will use a generalized linear mixed model for each outcome that incorporates fixed effects for time and treatment phase and a random effect for the individual practice site. We will use a similar mixed model for our primary implementation outcome (Reach; [24, 54, 67, 68]. The treatment variable will be specified as a binary variable corresponding to study phase (pre- and post-Active Implementation). We will estimate the model using restricted maximum likelihood. First, we will examine the effect of treatment on the outcome in an unadjusted analysis. Second, we will conduct an analysis adjusting for patient characteristics: age, sex, race/ethnicity, comorbidities (Charlson comorbidity score; [69]), presence of cognitive impairment (diagnosis of dementia; [70]), or functional impairment (JEN frailty index score; [71]). Third, we will conduct an analysis that also includes practice-level characteristics that may be confounders (number of Veterans served by the site, presence of a surgical program, presence of a pharmacy, urban/rural location, whether site is VA-operated or contracted). Then, because we hypothesize that Veterans at highest risk may benefit most from an AFHS, we will repeat our analyses in subgroups of Veterans who are in a cohort of High-Risk, High-Need Veterans identified by the Geriatrics and Extended Care and the Geriatrics and Extended Care Data Analysis Center as being at highest risk of death and long-term institutionalization in a nursing home. Last, consistent with PRISM, we will also seek to identify the “how and why” of implementation testing for mediating site variables [72] such as the PACT implementation index score [73], elements of the VA All Employee Survey, baseline Strategic Analytics for Improvement and Learning (or SAIL) ratings, whether any leadership positions were vacant or changed during implementation, and Practice Environment Scale of the Nursing Work Index. For all analysis, we will cluster errors by site, potentially with cluster bootstrap procedure to account for a small number of clusters.

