### Study goals and objectives

Our goals in the SAGE QUERI are threefold: (1) to compare different implementation strategies in a randomized fashion to understand how the interaction between implementation strategies, local site context, and intervention characteristics lead to different implementation outcomes; (2) to measure the impact of the implementation of evidence-based practices (or EBPs) on outcomes of older Veterans who are community dwelling; and (3) understand how these EBPs can most successfully be adapted for the VA context to allow successful national dissemination and maintenance in clinical practice.

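### The hypothesis that the highest-risk Veterans benefit most is tested only by refitting the model inside that group, and a baseline site rating is listed as a mediator

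*Protocol article*

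**What the plan says.** **Subgroup.** The Quantitative evaluation section of the protocol article gives its reason and its analysis in one sentence: "because we hypothesize that Veterans at highest risk may benefit most from an AFHS, we will repeat our analyses in subgroups of Veterans" in the High-Risk, High-Need cohort. The model to be repeated is one that "incorporates fixed effects for time and treatment phase and a random effect for the individual practice site". It has main effects only. The article names no treatment-by-risk term, no lower-risk comparison group and no contrast between groups.

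**Site variables.** The first aim under Study goals and objectives is to "understand how the interaction between implementation strategies, local site context, and intervention characteristics lead to different implementation outcomes". The quantitative analysis offered for the how and why is described in the Quantitative evaluation section as "of implementation testing for mediating site variables". Five kinds of variable are listed: the PACT implementation index, All Employee Survey elements, "baseline Strategic Analytics for Improvement and Learning (or SAIL) ratings", leadership vacancy or turnover during implementation, and the Practice Environment Scale. The Discussion again speaks of PRISM factors that may mediate outcomes. Practice-level characteristics also enter the third adjusted model, but as possible confounders and not as modifiers of the treatment effect.

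**The concern.** Both questions concern effect modification, and both are paired with an analysis that does not estimate it.

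For the subgroup, whether one group gains more can be judged only against the other group. A significant result inside the High-Risk, High-Need cohort is just what a uniform effect would also produce, so it is not evidence for the hypothesis. A non-significant result may reflect no more than the smaller sample.

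For the site variables, mediation needs a path from the strategy to the variable. A rating recorded before the strategy begins has no such path. What a baseline rating can do is alter how well the strategy works, which is the interaction that goal 1 describes.

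At stake is whether two stated explanatory questions receive a usable quantitative answer. The estimate of the main treatment effect is not at stake.

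**Working it through.** **1. The protocol's own figure.** The Power analysis section gives nine clusters, four periods, an SD of 0.84, a between-cluster term of 11.6 days, an average of 611 Veterans per VAMC, and a detectable change of 1.7 days at 80% power. Alpha is not stated; 0.05 two-sided is assumed. The Overview of study design gives three steps of three sites. With I = 9, T = 4, U = 18, W = 126 and V = 42, the standard stepped-wedge (Hussey–Hughes) variance is

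Var = I·s²(s² + T·τ²) / [(IU − W)s² + (U² + ITU − TW − IV)τ²] = 9s²(s² + 4τ²) / (36s² + 90τ²),

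where s² is the individual variance divided by the number per cluster-period (611/4 ≈ 153).

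- As printed (individual SD 0.84, between-cluster SD 11.6): detectable effect 0.12 days.
- Roles swapped (individual SD 11.6, between-cluster SD 0.84): 1.56 days, with power 86.5% at 1.7 days.

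Neither reproduces 1.7 days at 80%. That is a separate matter. Below, 1.7 days is taken at face value only to set a scale.

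**2. Implied precision.** Full-sample SE = 1.7 / (1.96 + 0.84) = 1.7 / 2.80 = 0.607 days.

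**3. Scaling to the subgroup.** The article does not give the High-Risk, High-Need share p, so a range is shown. If individual variance dominates and is equal in both groups:

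- SE in the subgroup = 0.607/√p; SE in the rest = 0.607/√(1 − p).
- SE of the difference = root sum of squares = 0.607/√(p(1 − p)).
- Detectable effect at 80% power: 1.7/√p in the subgroup and 1.7/√(p(1 − p)) for the difference.
- Probability that the subgroup is significant under a uniform effect d: Φ(d/SE − 1.96).

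The Power analysis section treats 6 days as meaningful, so d = 6. For p = 10%: SE = 0.607/0.316 = 1.92; 6/1.92 − 1.96 = 1.17; Φ = 0.88.

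| Assumed share | Subgroup SE (days) | P(subgroup significant), uniform 6 days | Detectable effect in subgroup (days) | Detectable difference (days) |
|---|---|---|---|---|
| 5% | 2.71 | 0.60 | 7.6 | 7.8 |
| 10% | 1.92 | 0.88 | 5.4 | 5.7 |
| 20% | 1.36 | 0.99 | 3.8 | 4.25 |
| 30% | 1.11 | about 1.00 | 3.1 | 3.7 |
| 50% | 0.86 | about 1.00 | 2.4 | 3.4 |

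In every row the true difference between groups is zero, and a valid interaction test would reject 5% of the time. With a smaller uniform effect at a 10% share, the subgroup refit is significant with probability 0.35 (3 days) or 0.14 (1.7 days).

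**4. The baseline mediator.** Indirect effect = a·b, where a is the effect of the strategy on the mediator. For a site rating fixed before Active Implementation, a = 0, so a·b = 0 whatever b is. In 2,000 simulated 9-site, 4-period trials with a baseline trait that strongly modified the effect, the site-adjusted indirect effect never exceeded about 4 × 10⁻¹⁵ in absolute value. A treatment-by-trait term in the same data was significant in 97% of runs. The 97% reflects a large illustrative effect and is not a power claim for this trial. It shows that the two analyses answer different questions.

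**The case against.** **The article is a condensation.** It does not say that significance inside the subgroup will be taken as proof of greater benefit. The full-cohort estimate will stand beside the subgroup estimate, and an unseen SAP may add a contrast. This stands as far as it goes: a reader might infer that the trial intends the misreading, and the text does not say so. But the article is not silent on the analysis. It states a comparative hypothesis and names an analysis without a comparison. The full-cohort estimate is no substitute, because it contains the subgroup and no test of the difference is named.

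**Only one listed variable is labelled baseline.** This stands. A reader might infer that all the site variables are baseline traits wrongly called mediators. The document does not support that. Leadership turnover occurs during implementation, and no timing is given for the PACT index, the employee survey or the Practice Environment Scale. Facilitation works through staff and leaders, so some of these could lie on its pathway.

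**Goal 1 does not rest on this test.** This also stands. A reader might infer that the goal goes unanswered. The pre-implementation contextual inquiry, the implementation tracking and interviews, and the mixed-methods evaluation all bear on it. Only the quantitative test through a pre-start variable is unsuitable.

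**An interaction test would be weak.** It would be. At a 10% share, a true contrast of 6 days against 1.7 days would be detected with power of only about 0.57, and at 20% about 0.81. An imprecise estimate of the right quantity, with its interval, is still more use than a precise estimate of a different one. The same calculation tempers worry about subgroup nulls: at a 10% share the subgroup's detectable effect, 5.4 days, is below 6 days.

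**Conclusion.** The point holds in a limited form. The refit in the High-Risk, High-Need cohort cannot show that this group benefits most: under a uniform 6-day effect it would be significant about 88% of the time at a 10% share (60% at 5%, 99% at 20%). These figures rest on the stated 1.7 days, which could not be reproduced, on two-sided alpha 0.05, on an assumed share, and on equal variances with no small-cluster correction. More variable outcomes among high-risk Veterans would lower the percentages but not change the logic.

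Baseline SAIL cannot be a mediator, and this needs no numerical assumption. The documents do not support extending that to the other listed site variables. These are explanatory analyses, so the matter should be corrected but is not critical.

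**What to change.** - In the full cohort, add a treatment-by-High-Risk, High-Need interaction, with membership fixed before each Veteran's index date. Report the effect in both groups and their difference with its interval.
- State when each listed site variable is measured. Analyse baseline SAIL, and any other that is in fact measured before Active Implementation, as a treatment-by-site moderator, one at a time and labelled exploratory because there are nine sites.
- Keep mediation for variables measured after Active Implementation starts that facilitation could change.

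The cost is one interaction term, the exploratory moderator terms and some rewording, with no new data and no design change. The drawback is imprecision: detectable differences of about 5.7 days at a 10% share and 4.25 at 20%, both optimistic with nine clusters. They should be reported as such.

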#### Economic evaluation business case

In the interest of improving the value of care along with effectiveness, we will conduct a budget impact analysis (BIA), which relates closely to a standard cost-effectiveness analysis but allows for the examination of shorter-term use of health care resources (over 1–3 years) as a value metric. A BIA approach was selected because it focuses exclusively on downstream costs of implementing 4Ms from the perspective of the VA. This outcome represents an ideal measure of value for our target population: all four EBPs are focused on increasing facility-free days and decreasing health care utilization. Further, this outcome can be fully and accurately measured with the data gathered during our Evaluation phase, allowing for accurate measurement of costs for both Active Implementation and Implementation as Usual phases. We will follow best practices for data reporting, including showing the cost of each intervention and total costs; costs or savings from downstream healthcare use for participants; and the implementation costs of the for EBPs [74]. For example, we will factor in the cost of time required of implementation staff through VA personnel data (e.g., wages, hours worked, additional staff needed) and project records, and capture changes in how processes are conducted (and potential time savings) across sites through comparison of pre-Implementation to post-Active Implementation process maps.

## Discussion

The overall goal of the SAGE QUERI program is to understand how best to implement and scale evidence-based practices aligned with the AFHS model within the VA. SAGE QUERI expands on prior Age-Friendly work by identifying four evidence-based interventions to address core tenets (4Ms) of the AFHS initiative, rigorously evaluating different implementation strategies, and assessing a clinically meaningful outcome across all four EBPs. The primary outcome—“facility free days”—is aligned with the goals of older adults to live independently in the community as they age, and with system and payer needs to reduce costs. We will test the effectiveness of implementation strategies of implementation as usual compared with external facilitation, training and technical assistance, intervention tailoring, and audit and feedback, while providing valuable information about the cost effectiveness of each intervention. Together, the SAGE QUERI program will provide an implementation model of AFHS-concordant care across an entire regional healthcare system, offering insights for replication across the VA in fulfillment of its operational commitment to becoming a nation-wide AHFS.

Notable strengths of the study methods and designs include our robust application of the PRISM framework, as well as our interdisciplinary mixed method approaches are designed to identify contextual factors to fit implementation strategies with local sites’ needs and preferences (Table 1). The framework also allows us to leverage the RE-AIM model to generate ongoing feedback during the study and analyze patient and implementation outcomes (Table 2). The use of a randomized type III hybrid effectiveness implementation study with a stepped wedge design will allow us to measure the impact of implementation of evidence-based practices aligned with the AFHS model on outcomes of older Veterans. Our quantitative “realist” evaluation will draw inferences about factors identified from the PRISM framework that may mediate implementation and effectiveness outcomes and quantify the costs relative to outcomes achieved. Likewise, the PRISM framework will inform the identification of internal and external implementation barriers and facilitators for each EBP at the staff, provider, and patient level through stakeholder interviews, observations, and focus groups. This will allow us to tailor and adapt EBPs to address barriers and optimize facilitators to fit the local contexts. Drawing on a wide range of qualitative approaches and will provide critical insight into best implementation practices and how these may vary by context.

Although all included EBPs have been previously tested in other settings, to our knowledge, none are part of routine care within VISN 4, or in the VA. As a result, we anticipate significant challenges to implementation and adaptation. For example, for TAP and CAPABLE, one anticipated challenge is first identifying where the EBPs will best fit within each site and who will implement the interventions, as there are a range of potential implementation settings (Table 3). In addition, the VA has robust home care programs (such as Home-Based Primary Care) that stakeholders may perceive as duplicating these efforts (or, alternatively, providing a useful platform for implementing them). Coordination of implementation may be challenging because it is difficult to engage stakeholders who cross multiple departments and settings [14]. Similarly, Surgical Pause requires close coordination between surgeons, palliative care clinicians, and pre-operative clinics that could include other staff (e.g., general internists, anesthesiologists), making implementation more complex.

A second set of potential challenges is that sites may not choose to implement all four EBPs, despite our hypothesis that implementing all four EBPs are likely to have synergistic effects across the 4Ms, and thus a greater impact on the primary clinical and implementation outcomes. To increase feasibility of adoption for each medical center, we have conceptualized and chosen EBPs that do not rely on a single site of practice (e.g., primary care or geriatrics departments) to be responsible for implementing all four interventions. Our goal is to have the EBPs employed in every clinical setting to which they apply (for example, Surgical Pause could be disseminated to inpatient surgery and to non-surgical procedural specialties) in the nature of the AFHS model. In addition, we strategically selected EBPs that align with VA national initiatives. Additionally, using preliminary data, we identified potential adaptations to the interventions that may overcome these barriers. For example, the TAP and CAPABLE models are led by occupational therapists (OTs). The VA employs OTs and also contracts with OTs employed by outside agencies to provide home-based care for Veterans. We thus have the option to implement these interventions using VA staff or by training contracted staff. These decisions have trade-offs but contribute to the rich contextual inquiry and are likely applicable trade-offs to other VA sites—such as generating knowledge to medical centers that differ in approaches for employing OTs.

Finally, we anticipate the VA—like all health systems—is dealing with the effects of the COVID-19 pandemic. We are already seeing disruptions due to the COVID-19 pandemic impacting our early pre-implementation data collection (e.g., limit ability to travel to sites) and anticipate it will impact the implementation phases (e.g., create competing priorities, reduce staff capacity, interfere with in-person intervention delivery). To overcome disruptions to data collection during the pre-implementation phase, we have incorporated ongoing pandemic-related challenges into our protocol with the knowledge that things will continue to change as variants/waves increase/decrease over time. For example, we created a modified hybrid approach that is allowing us to conduct site visits in person, virtually, or a mixture of both. Additionally, given potential limited capacity of SAGE team to travel, we anticipate the potential of being able to partner with sites’ local quality improvement departments, high-reliability leaders, and/or Whole Health staff (an established VA initiative centered around well-being of Veterans) to gather data and/or assist with the implementation process [20]. We will also monitor and track how the interventions are adapted to address ongoing disruptions due to the pandemic. It is clear that after 2 years of the COVID-19 pandemic, there is great need to identify novel to promote remote implementation strategies. In fact, we anticipate this will be an important value added to the field of implementation science as we spread these EBPs broadly during a pandemic.

## Anticipated contributions to practice

To our knowledge, this is the first large-scale randomized effort to implement AFHS aligned evidence-based practices in a national health care system. Given the pressing need to improve care delivery for older adults, we anticipate findings from this project will be timely and relevant. Deliverables include not just knowledge about how each EBP might be most successfully disseminated and implemented in the VA, but how they might affect novel outcomes (e.g., days at home), how each varies in terms of costs and changes in outcomes, and best practices for expansion beyond VISN 4 (even within a pandemic). Although this work was designed to be implemented internally within the VA for operational purposes, we plan to partner with the IHI and the John A. Hartford Foundation, as well as our Veteran Advisory Board and Technical Expert Panel, to create and deliver VA-specific toolkits hosted by IHI and the John A. Hartford Foundation on the national Age-Friendly initiative website, as well as on the websites of our national VA partners (GEC and National Surgical Office). We will also deliver VA-specific toolkits to be hosted by the Canadian Deprescribing Network and by TAP and CAPABLE directors and institutions. Each toolkit will contain a collection of materials including written documents, videos, and links aimed at educating VA leadership and clinicians about the AFHS model and implementation of each of the four EBPs. We will also incorporate materials designed for use in our Implementation as Usual phase, to assist future users in spreading the AFHS approach. Moreover, we will create “patient-facing” guides as a resource for Veterans and caregivers; emerging evidence suggests these resources can act as a “pull” mechanism for Dissemination as they create demand in the targeted populations [75]. Ultimately, we plan on reaching out to other VISNs with the goal of spreading these EBP nationally.

## Data Availability

The datasets generated and/or analyzed during the current study are not publicly available due to identifying nature of patients and providers who participated in the qualitative data collection. Furthermore, the VA claim data has patient data that is not to be shared publicly. However, how data was collected and managed can be shared including the interview guides via the corresponding author on reasonable request.

## Abbreviations

ADL: Activities of Daily Living
AFHS: Age-Friendly Health System
BIA: Budget impact analysis
CPT: Current Procedural Terminology
EBP: Evidence-based practice
EMPOWER: Eliminating Medications Through Patient Ownership of End Results
IHI: Institute for Healthcare Improvement
OT: Occupational therapist
PRISM: Pragmatic Robust Implementation and Sustainability Model
QUERI: Quality Enhancement Research Initiative
RE-AIM: Reach Effectiveness-Adoption Implementation Maintenance
SAGE: Safer Aging through Geriatrics-Informed Evidence-Based Practices
SAIL: Strategic Analytics for Improvement and Learning
TAP: Tailored Activities Program
VA: Veterans Affairs
VAMC: VA medical centers
VASQIP: Veterans Affairs Surgical Quality Improvement Program
VISN: Veteran Integrated Service Network
